### Trial design

The trial is a two-arm parallel group multicentre pragmatic superiority randomized controlled trial (RCT), with a 1:1 allocation at the individual level. The group SMS intervention will be offered to participants in the TAU groups after the 12-month follow-up (delayed-intervention). The 24-month follow-up will therefore only provide a within-group dataset. The proposed protocol conforms to SPIRIT guidance [40].

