## Methods

### Participants, interventions, and outcomes

#### Study setting

The study will be conducted in four health administrative regions in Quebec (Canada): Eastern townships, Mauricie-et-Centre-du-Québec, Abitibi-Témiscamingue and Laurentides. Administrative regions were purposefully selected based on the following criteria: a) the in-person group SMS intervention is not currently largely implemented in the region; b) the virtual SMS intervention is rarely accessed by participants from the region, even though the virtual SMS format is technically accessible throughout the province; c) diversity (e.g., population size, region, university teaching hospital).

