#### Interventions

##### Group SMS for anxiety disorders + treatment-as-usual (TAU)

The SMS manualized program for anxiety disorders (https://monrelief.ca) aims at improving self-management capabilities through weekly 2.5-h sessions with 10–15 patients over a 10-week period. The SMS program (see Table 1) covers the following themes: getting to know your anxiety; building self-awareness; reconsidering your lifestyle habits; adopting a problem-solving method; avoidance and exposure; acceptance and committed action; seeing things differently; managing your emotions; receiving support from others; and consolidating your toolkit. The trial will focus solely on the virtual format. As in the groups delivered by Relief, SMS will be either co-facilitated by health care professionals (e.g., social worker, psycho-educator, nurse), or by a health care professional and a peer supporter, namely a person recovered from an anxiety disorder who has experience and training offering peer support, building on mutual understanding and respect [42–44], to emphasize experiential knowledge sharing. *Relief* will provide the material for the training of the facilitators, the program documentation, the eLearning platform, and the material used by the participants. Consistent with standard implementation of this SMS program, facilitators will participate in a one-day *Relief* training program. Three case discussions for each group delivered (before onset, mid-group, and following last session) will be conducted by the research team. A random review of 30% of recordings of sessions will be conducted to monitor adherence with a treatment integrity scale. Integrity data will not be used to intervene to improve compliance, but only to examine process-outcome correlation and to guide improvements following the trial. Patient compliance will be supported through the extensive Relief experience delivering SMS (e.g., material, training, support), and the convenient eLearning platform (e.g., easy access, reduced stigma).

**Table 1 Tab1:** Content of the 10-week SMS manualized group program for anxiety disorders

Week	Theme	Content
1	Getting to know your anxiety	• Learn more about anxiety • Recognize the signs of anxiety
2	Building self-awareness	• Develop self-observation skills to better understand your anxiety • Understand the function of different resources that are available

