##### Treatment-as-usual

No limitations will be imposed concerning usual care, as we aim at examining the added value of SMS to TAU. To reflect heterogeneity of health seeking behaviour and mental health practices for anxiety disorders in the community, we do not require that participants have a family physician, be constrained to a prespecified usual care or have contacts with the healthcare system. To minimize behavioural change in healthcare providers, we will not inform any healthcare provider of participation in the study. As the intervention will be provided on an eLearning platform, and not embedded in clinics, contact between intervention and control patients is unlikely. All participants will receive information about the SMS intervention and the goal of the study, i.e., “of helping them manage their anxiety”. We will thoroughly assess participant-reported service utilization 12 months prior to enrolment and during the study to examine risk of study-induced behavioral change with regards to usual care.

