#### Statistical Analyses

##### Clinical outcomes

Statistical analysis will follow intent-to-treat principles. The primary outcome analysis will be performed at T_1_. The remaining analysis will be conducted considering all measures over time when all participants have completed the 12-month (T_0_ through T_3_) and 24-month follow up (T_0_ through T_4_). Primary question: A mixed model regression with the maximum-likelihood method will be performed to consider between- and within-subject variations in the analysis of the longitudinal effects of SMS + TAU compared to TAU on the primary outcome measure (BAI) at post-treatment (T_1_). To control for potential intra-group variability, random effects will be added on the participants nested in the SMS groups. Baseline clinical variables (e.g., anxiety disorders, comorbid depressive symptoms, psychotropic medication, psychotherapy) will be entered in the model as covariates. Analyses will be conducted with all available data without imputation, as estimation of parameters by maximum likelihood is considered adequate to address missing data as post-treatment in the multilevel model [74, 75].

For secondary questions, logistic regression models will be used to examine high-end functioning rates. The mixed model regression approach will be repeated on all data at the 12-month (T_0_ through T_3_) and 24-month (T_0_ through T_4_) follow-up, and will allow for the inclusion of patients with missing data at any of the follow-up assessments (T_1_,T_2_,T_3_,T_4_). Additionally, treatment effect sizes will be estimated with Cohen’s *d*. We will also conduct hypothesis-generating moderator and mediator analysis [76]. Moderation analyses will be performed for three sets of moderators, including clinical characteristics (e.g., anxiety disorders at baseline, anxiety severity, comorbid depression), previous treatments (psychotropic medication, psychotherapy) and sociodemographic characteristics (e.g., age group, sex, education level). Mediators will be examined for therapeutic alliance, group cohesion and adherence. Sensitivity analysis will be applied to examine the influence of missing data, and to document *per protocol* treatment effects (≥ 8 sessions completed).

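### The per-protocol sensitivity analysis is defined only by SMS attendance after randomisation, so on its ordinary reading it mixes selection of engaged patients with the effect of attending

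*Protocol article*

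**What the plan says.** In the Protocol article, Statistical Analyses, Clinical outcomes, the governing rule is "Statistical analysis will follow intent-to-treat principles", and the primary analysis is a mixed model of the BAI at T1. The same section ends with the plan in question: "Sensitivity analysis will be applied to examine the influence of missing data, and to document" per-protocol treatment effects, with at least "8 sessions completed" as the criterion. The section gives no other criterion, comparison group or estimator for this analysis.

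Four other sections bear on it:

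- **Group SMS for anxiety disorders + treatment-as-usual (TAU):** the programme consists of "weekly 2.5-h sessions with 10–15 patients over a 10-week period".
- **Treatment-as-usual:** "No limitations will be imposed concerning usual care".
- **Trial design:** "The group SMS intervention will be offered to participants in the TAU groups after the 12-month follow-up".
- **Questionnaires completed during SMS sessions:** facilitators record each participant's adherence in a logbook.

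**The concern.** A count of SMS sessions is known only after randomisation, and during the controlled period the trial generates it in one arm only. TAU patients have no sessions to complete and no adherence rule of their own. If the analysis keeps SMS patients with 8 or more sessions and sets them against all TAU patients, the first group has been selected on engagement and the second has not. TAU still contains those who would have dropped out of the programme.

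The difference then has two parts: the effect of attending, and the difference in course between patients who stay with a weekly group and patients who do not. The data cannot separate them. The baseline clinical covariates are stated for the primary model. If carried over they could reduce the second part, but they would not reliably remove it. Participants are unmasked and the BAI is self-reported, so motivation may plausibly be related to the score.

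At stake is the meaning of a secondary number. The term per-protocol treatment effect invites a causal reading, and on this construction the number would not support one.

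**Working it through.** **The plan's own figures.** The article states none for the per-protocol analysis. The yardstick is the design difference in the Sample size section: 4 BAI points with SD 12.5, so d = 4/12.5 = 0.32. A two-sided two-sample t-test at alpha 0.05 and 80% power needs 154.26, hence 155 per group, and 155/0.75 = 206.7, hence 207 per arm. Both match the article, and no stated number is wrong.

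**Form of the bias.** Let p be the share of patients who would complete 8 or more sessions if offered SMS. Let delta be the T1 BAI difference under TAU between would-be completers and the rest, taken as positive when would-be completers do better. The TAU arm is a mixture of the two, so

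bias = m_c - [p m_c + (1-p) m_n] = (1-p)(m_c - m_n) = (1-p) x delta,

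where m_c and m_n are the mean improvements under TAU of would-be completers and non-completers.

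**Numbers.** Neither p nor delta is in the article. Assume p = 0.6 to 0.75 and delta = 2 to 4 points.

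- Lowest: (1-0.75) x 2 = 0.5 points
- Highest: (1-0.6) x 4 = 1.6 points
- Relative to the 4-point design difference: 0.5/4 = 13% and 1.6/4 = 40%

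**Second route.** Suppose a normal engagement score correlates rho with untreated improvement, and the top share c completes. Then bias = rho x 12.5 x phi(z)/c, where phi is the standard normal density and z is the (1-c) quantile. The values of c and rho are again assumed.

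| c | rho 0.1 | rho 0.2 | rho 0.3 |
|---|---|---|---|
| 0.6 | 0.80 | 1.61 | 2.41 |
| 0.7 | 0.62 | 1.24 | 1.86 |
| 0.8 | 0.44 | 0.87 | 1.31 |

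With no true effect, 155 per arm, no covariates and no clustering, 4,000 simulated trials per setting at c = 0.7 gave rejection rates of 6.6%, 12.2% and 23.0% for rho 0.1, 0.2 and 0.3, at a nominal 5%. With rho = 0 there was no bias, and the rate was 5.3%.

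**Check of the remedy.** A complier average effect divides the intention-to-treat difference by the difference in receipt. This requires that assignment has no effect except through receipt. Suppose receipt is taken as 8 or more sessions, completers gain 4 points and all others attend in part and gain 2 (assumed).

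- p = 0.6: ITT = 0.6 x 4 + 0.4 x 2 = 3.2; 3.2/0.6 = 5.3; overstatement 1.3
- p = 0.75: ITT = 0.75 x 4 + 0.25 x 2 = 3.5; 3.5/0.75 = 4.7; overstatement 0.7

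An instrumented 8-session variable can therefore err by 0.7 to 1.3 points, about as much as the bias it is meant to remove. Defining receipt as at least one session avoids this, because partial attenders then count as having received the programme.

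**The case against.** The strongest objection is that the article never says SMS completers will be compared with all TAU patients. It gives a threshold and nothing more, and a randomisation-respecting estimator with 8 sessions as the receipt definition would also fit the sentence. Such detail is commonly left to an analysis plan, and one may exist. This stands in part. The comparison is the natural meaning of a per-protocol effect, but it is a reading. What the article does fix is a definition by SMS attendance alone, and that is enough to ask for confirmation or change.

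The analysis is also a sensitivity analysis behind an intention-to-treat primary. A reader might infer that the trial's main conclusion is at risk. The documents do not support that, since no hypothesis or sample size depends on this estimate. Nor do they say that it would be reported as the effect of receiving the programme.

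A reader might also infer that the bias must favour SMS. Patients who improve early may stop attending, which would reverse the sign.

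Finally, a reader might infer material uptake of the programme in TAU from the Study setting remark "even though the virtual SMS format is technically accessible throughout the province". The same sentence says that regions were chosen because residents rarely use the virtual programme. Previous enrolment is an exclusion criterion, and service use is to be assessed during the study. Uptake is therefore something to count if it occurs, and not a demonstrated flaw.

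**Conclusion.** The point holds in limited form. The per-protocol criterion is measured after randomisation and has no TAU counterpart, so on its ordinary reading the estimate loses the protection of randomisation. The primary result is untouched, and the severity is low.

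The 0.5-1.6 point range, and its 13-40% share of the design difference, rest wholly on assumed completion and prognosis and on no covariate adjustment. They show that the bias could matter, not that it will. It would be nil if engagement were unrelated to prognosis, and its direction is not established.

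**What to change.** 1. Make a complier average causal effect the lead estimate of the effect of attendance, with randomisation as the instrument and the primary model's covariates. Define receipt as at least one session, or as the number of sessions attended (0-10), from the facilitator logbook.
2. Do not use 8 or more sessions as the binary receipt variable, because benefit from partial attendance breaks the exclusion restriction.
3. Keep the 8-session completer comparison as a descriptive analysis, state its comparison group, and do not call it a treatment effect.
4. Count as receipt any TAU use of the programme found in the participant-reported service-use data. The article describes that questionnaire only in outline, so check that it would capture such use.

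If an analysis plan already specifies a randomisation-respecting estimator, it is enough to confirm that its receipt definition meets point 2.

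Cost: one further analysis on data already planned. The confidence interval will be wider than for intention-to-treat, because the difference is divided by a receipt share below 1. The exclusion restriction must be stated; with an unmasked, self-reported outcome it is an assumption even for the one-session definition. The 0-10 version also assumes that benefit is linear in sessions. The one-session version estimates the average effect among those who attend at all, not the effect of a full course, and should be described so.

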##### Economic evaluation outcomes

The cost-effectiveness and cost-utility analysis will be carried out from health system and patient perspectives based on Canadian guidelines [77]. The 2-year costs considered will include all medical services and resources used during hospitalization, emergency department visits, outpatient visits, physician fees and outpatient medications. Patient out-of-pocket costs will include drug co-payments, payments to professionals not covered by the provincial public health insurance coverage, costs related to transportation and time spent by patients while seeking outpatient medical attention, as well as costs related to presenteeism and absenteeism [78]. Program costs associated with the training of facilitators and group meetings will include salaries, benefits, institutional overhead, and opportunity costs [79]. Generalized linear models (GLM) with log link and appropriate distribution (i.e., gamma) will be used to study the difference in costs (Beta estimates) as a function of the intervention (TAU vs SMS) while controlling for potential confounding study factors. Health outcomes will include symptom reduction (BAI) and health-related multi-attribute utility quality of life (AQoL-6D). The number of Anxiety-Free Days (AFD) will be calculated for each BAI scores with a value between 1 (‘anxiety free’) and 0 (‘fully symptomatic’) with linear interpolation to estimate the number of AFDs between baseline and follow up [80]. We will measure quality of life with the AQoL-6D to assess utility estimates [81]. For data analyses, repeated measures will be used to assess the difference (Beta estimates) in health outcomes as a function of the intervention and variables of interest. The incremental cost-effectiveness ratios (ICER) and incremental cost-utility ratios (ICUR) will be calculated based on beta estimates obtained. A discounting rate of 3.5% will be used for future values. We will carry out a sensitivity analysis for estimated values while considering a range of plausible values (95% CI). The ICUR will quantify the trade-off between costs and health-related quality of life.

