### Objectives

The aim of the present study is to evaluate the effectiveness of a structured group virtual SMS program as an add-on to treatment-as-usual (TAU) in a sample of adults with anxiety disorders. Primary questions: When group SMS is added to TAU in community-based care for patients with anxiety disorders, is the SMS + TAU group more effective in reducing anxiety symptoms than TAU alone? Secondary questions: a) Considering a recovery-oriented approach for patients with anxiety disorders, is there a significant difference between group SMS + TAU and usual care in terms of self-management strategies and personal recovery assessment at the 12-month follow-up? b) Does group SMS + TAU present superior cost-effectiveness and cost-utility, in terms of quality of life and anxiety-free days, than TAU for patients with anxiety disorders at the 12-months follow-up? c) Is there a significant difference between group SMS + TAU and usual care for high-end functioning rates? d) Is there maintenance of gains at 12- and 24-months follow-up? e) Is there differential effectiveness based on moderators (i.e., sociodemographic characteristics, clinical characteristics, past treatment experience) and mediators (i.e., group cohesion, therapeutic alliance, adherence)?

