**ECONOMIC EVALUATION OUTCOMES**							
AQoL-6D		X		X	X	X	X
Service utilization and medication (past 4-months)		X		X	X	X	X

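### The economic analysis compares 2-year costs between arms, but its objective is set at 12 months and controls are offered SMS after month 12

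*Protocol article*

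**What the plan says.** Four places in the protocol article bear on the horizon of the economic evaluation.

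- **Objectives, secondary question (b).** Superior cost-effectiveness and cost-utility are to be examined "in terms of quality of life and anxiety-free days, than TAU for patients with anxiety disorders at the 12-months follow-up".
- **Trial design.** TAU participants are offered the SMS programme once the 12-month follow-up is done. The section draws the consequence itself: "The 24-month follow-up will therefore only provide a within-group dataset".
- **Economic evaluation outcomes.** "The 2-year costs considered will include all medical services and resources used during hospitalization", together with emergency, outpatient, physician and medication costs. Cost differences are modelled "as a function of the intervention (TAU vs SMS) while controlling for potential confounding study factors", and the ICER and ICUR are built from the resulting estimates. "A discounting rate of 3.5% will be used for future values".
- **Table 2, economic evaluation block.** The row whose label begins "Service utilization and medication (past 4-months" is marked at T0, T1, T2, T3 and T4. The Participant timeline puts T1 to T4 at months 4, 8, 12 and 24.

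The Service utilization section adds that provincial databases supply medical and biopsychosocial services, emergency, hospitalization and medication data. A brief questionnaire covers other mental health consultations and psychotropic medication, to make up for what the databases lack.

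**The concern.** The horizon in the economic section does not match the objective it serves, and it uses year-2 data in a way the design section rules out. Up to month 12 the randomised contrast is SMS + TAU against TAU. After that, control participants may receive the programme, so a difference accumulated to month 24 is partly a difference between starting early and starting late.

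An ICER or ICUR on that basis would not give the added value of SMS over usual care, which is what question (b) asks and what the Discussion says could influence stakeholders' decisions. Leaving both horizons in the text would also allow 12 or 24 months to be chosen after the results are seen.

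A second, smaller issue is whether self-reported costs can be accumulated over 2 years at all, given a 4-month recall and a 12-month interval between T3 and T4.

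**Working it through.** The plan gives no computed figure on this point, so the check sets the passages side by side and maps the recall windows.

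**1. Which contrast does each period carry?**
- Months 0–12: SMS + TAU versus TAU, as randomised. This matches question (b).
- Months 12–24: SMS already received versus SMS on offer, that is, immediate versus delayed. The Trial design section treats these data as within-group.
- Share of a 2-year horizon that follows the offer to controls: 12/24 = 50%.

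**2. Does any reading reconcile the 2-year costs with the rest?**
- *Costs and effects both over 24 months.* The second half is immediate versus delayed SMS. Anxiety-free days would also be linearly interpolated across the 12 months from T3 to T4, with no assessment in between, while controls may be attending the programme.
- *Costs over 24 months, effects over 12.* The numerator and denominator of the ratio would cover different periods.
- *12 months before plus 12 months after enrolment.* Service use in the prior 12 months is collected at baseline, so this is conceivable. The text does not say it, though, and discounting future values at 3.5% points to a horizon beyond one year after enrolment.

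None of the three gives a 2-year between-arm analysis that agrees with both the Objectives and the Trial design.

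**3. Questionnaire coverage.** Each window runs from (visit month − 4) to the visit month.
- T1: months 0–4
- T2: months 4–8
- T3: months 8–12
- T4: months 20–24

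Coverage of 0–24 months is 4 × 4 = 16 months. The gap is 24 − 16 = 8 months (months 12–20), which is 8/24 = 33% of the horizon and 8/12 = 67% of year 2. Coverage of 0–12 months is 3 × 4 = 12 of 12 months, with no gap.

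**4. What the gap touches.**
- *Not affected:* services and medication taken from the administrative databases, which have no 4-month recall limit. The Participant timeline section calls this dataset complete for service utilization.
- *Affected:* consultations with professionals outside public coverage.
- *Probably affected:* travel, time, presenteeism and absenteeism costs. This is an inference, because the article does not give the questionnaire's full content.

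**5. Programme cost (illustration only).** Let u be the share of controls who take up delayed SMS. Suppose that delayed delivery is charged to the TAU arm, the SMS arm has full uptake, the cost per participant is equal and discounting is ignored. The incremental programme cost at 24 months is then (1 − u) of its 12-month value: 100% at u = 0, 50% at u = 0.5, 20% at u = 0.8 and 0% at u = 1. The article gives no value for u and does not state the costing rule, so these figures show a direction and are not an estimate.

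**The case against.** The strongest reply is that the authors already recognise the limit. The Objectives fix the economic question at 12 months and the Trial design section says month 24 is within-group. On this view the economic section simply was not aligned with them, and a reader would know which comparison is meant. That explains how the mismatch arose, but it does not remove it. The economic section is the operative text, and it names a TAU-versus-SMS contrast, 2-year costs and discounting together.

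Other objections narrow the point, and they stand.

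- A reader might infer that months 12–20 are unobserved. The documents do not support this. The items in the sentence that carries the 2-year horizon are largely those the administrative databases supply. The following sentence, on out-of-pocket and productivity costs, states no horizon of its own.
- A reader might infer that a 2-year ICER would charge programme costs to both arms. The article lists training and group-meeting costs but does not say whether delayed delivery is costed. The fault is the missing rule.
- The T4 recall window rests on one table label. The questionnaire is not shown, and its T4 wording may differ. The gap is a literal reading to be clarified, and does not prove that self-reported costs would be understated.
- The horizon for effects is given only as running from baseline to follow-up, so a 24-month effect horizon is not stated either.

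**Conclusion.** The point holds as an internal contradiction. Modelling 2-year costs between arms conflicts with the 12-month economic objective and with the statement that month 24 gives only within-group data. Half of the 2-year horizon follows the offer of SMS to controls, and the article has no rule for costing delayed SMS.

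The recall gap of 8 of 24 months is right for questionnaire data if the Table 2 label applies at T4 as printed. It is confined to costs that depend on self-report. The size of any distortion in the ICER or ICUR cannot be derived from the document, because neither uptake among controls nor the costing rule is given.

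This should be fixed. It affects a named secondary objective, while the primary BAI analysis at T1 is untouched and the data needed for a 12-month economic analysis are fully planned.

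**What to change.** 1. State in the economic section that the between-arm ICER and ICUR cover months 0–12 for both costs and effects. This matches question (b), keeps the randomised contrast, has complete questionnaire coverage and needs no discounting.
2. Report months 12–24 descriptively, within group, or as a comparison explicitly labelled immediate versus delayed SMS. If that comparison is made, state how delayed SMS in controls is costed, and keep the 3.5% discounting for this part only.
3. For year-2 costs, either limit them to administrative data or widen the T4 recall to the whole period since T3.

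Items 1 and 2 are wording changes and cost no data. Widening the T4 recall is a one-line questionnaire edit, at the price of some added recall error over 12 months. Limiting year 2 to administrative data avoids that error but gives up the self-reported part of the patient perspective in that year. The horizon should be fixed before any economic data are analysed.

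### The ICER and ICUR are to be based on log-link cost betas described as cost differences, but such a beta is a log cost ratio with no dollar unit

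*Protocol article*

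**What the plan says.** All of the economic method is in Economic evaluation outcomes, under Statistical Analyses.

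- **Costs:** "Generalized linear models (GLM) with log link and appropriate distribution (i.e., gamma) will be used to study the difference in costs (Beta estimates"). The model is adjusted: "as a function of the intervention (TAU vs SMS) while controlling for potential confounding study factors".
- **Effects:** "repeated measures will be used to assess the difference (Beta estimates) in health outcomes as a function of the intervention". Anxiety-free days are derived from BAI scores and interpolated linearly between assessments. AQoL-6D supplies utilities; how these accumulate over time is not described.
- **Ratios:** "The incremental cost-effectiveness ratios (ICER) and incremental cost-utility ratios (ICUR) will be calculated based on beta estimates obtained".
- **Purpose:** "The ICUR will quantify the trade-off between costs and health-related quality of life".
- **Uncertainty:** "We will carry out a sensitivity analysis for estimated values while considering a range of plausible values (95% CI").

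Objectives, secondary question (b), asks about cost-effectiveness and cost-utility "in terms of quality of life and anxiety-free days" at 12 months. The economic section counts costs over two years. Trial design says that TAU participants are offered the programme after month 12 and that the 24-month data are within-group only.

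**The concern.** The sentence on costs puts the word beta in parentheses after the cost difference, as if the two were the same quantity. They would be under an identity link. Under the log link that the same sentence specifies, they are not. The sentence on the ratios then builds the ICER and ICUR from betas, and no step between the two returns the estimate to dollars.

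An analyst who follows the text literally would divide a unitless log ratio by a difference in utility or in anxiety-free days. The result could not be read as a price per unit of benefit or compared with a willingness-to-pay value. Secondary question (b) would go unanswered in the form in which decision makers need it. If the 95% CI used in the sensitivity analysis is that of the cost beta, it carries the same scale problem.

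**Working it through.** The article states no cost, ICER or ICUR, so there is no figure to reproduce. The check is algebraic, with illustrative values that are all assumptions.

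**1. What the beta is.** Under a log link,

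E[C | SMS + TAU] = E[C | TAU] × exp(β), so β = ln(mean cost SMS + TAU / mean cost TAU).

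This is a log ratio without a unit.

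**2. What the numerator needs.** Without covariates, the dollar increment is

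ΔC = μ_TAU × (exp(β) − 1).

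It depends on the TAU mean μ_TAU, which β does not contain. No fixed factor converts one into the other.

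**3. Illustration.** Assume a cost ratio of 1.10, so β = ln(1.10) = 0.0953, and an effect of 0.03 quality-adjusted years.

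| Assumed TAU mean | ΔC = mean × 0.10 | ΔC / 0.03 | β / 0.03 |
|---|---|---|---|
| $2,000 | $200 | $6,667 | 3.18 |
| $5,000 | $500 | $16,667 | 3.18 |
| $10,000 | $1,000 | $33,333 | 3.18 |

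The ratio in dollars changes fivefold while the ratio built on beta does not move.

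Conversely, hold the increment at $500 and the effect at 0.02. The dollar ratio is 500 / 0.02 = $25,000 in every case, but the beta ratio falls as the TAU mean rises:

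- $2,000: ln(2,500/2,000) / 0.02 = 0.2231 / 0.02 = 11.16
- $5,000: ln(5,500/5,000) / 0.02 = 0.0953 / 0.02 = 4.77
- $10,000: ln(10,500/10,000) / 0.02 = 0.0488 / 0.02 = 2.44

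The beta ratio can therefore vary when the true ratio is constant, and stay constant when the true ratio varies.

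**4. With covariates, as planned.** A gamma log-link GLM was fitted to simulated costs: 20,000 per arm, true cost ratio 1.10, mean cost $5,000 in TAU at covariate value zero, and one standard normal covariate with coefficient 0.5.

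- The fitted intercept was 8.512 and the fitted treatment beta 0.0909.
- Predicting every patient's cost under each arm and averaging the difference gave about $535. The true value in this set-up is 5,000 × exp(0.5²/2) × 0.10 = $567.
- Back-transforming at covariate value zero only gives exp(8.512) × (exp(0.0909) − 1) ≈ 4,976 × 0.0952 ≈ $473.

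Exponentiating beta alone is therefore not enough in an adjusted model. Predictions have to be averaged over the patients' covariates.

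**5. Time base.** Costs are sums over a period, so the effect must also be a sum over the same period. Anxiety-free days already are. A repeated-measures beta on AQoL-6D is a difference in utility level unless utilities are first accumulated. Table 2 schedules AQoL-6D at baseline and at 4, 8, 12 and 24 months, so an area under the curve is available to month 12 without new data.

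**The case against.** The strongest reply is that the ratios are only said to be based on the betas. Predicted arm means from a log-link GLM are also based on its betas. The section follows Canadian guidelines and wants a trade-off between costs and quality of life, so a numerator in dollars is plainly intended. A journal article may leave post-estimation detail to an analysis plan that is not shown.

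Part of this stands. The intention is probably right, and it cannot be said that the investigators will divide raw betas. But the article does more than omit a step: it labels the log-link beta as the cost difference, which is wrong, and nothing elsewhere corrects it. A fuller plan would have to contradict the sentence, not only add to it.

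A reader might infer three stronger criticisms that the document does not support:

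- **That the utility denominator is wrong.** The article does not define how AQoL-6D utility is accumulated. That is left open, not misstated, and anxiety-free days are explicitly interpolated over time.
- **That zero-cost patients will be lost from TAU only, biasing the incremental cost in favour of SMS.** The Treatment-as-usual section says "we do not require that participants have a family physician, be constrained to a prespecified usual care or have contacts with the healthcare system". This makes zero costs possible in the narrower health-system perspective, but it does not say that they occur or that such patients are excluded. The gamma log-link estimating equation uses (y − μ)/μ, which is defined at y = 0. Over the stated two years, TAU participants who accept the programme after month 12 would carry programme cost too. No zero share is given, so no bias can be sized.
- **That the uncertainty method is an error.** A two-part cost model, or a bootstrap that resamples SMS groups, is a reasonable option, but the article's text is not wrong for lacking it.

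**Conclusion.** The point holds in a narrow form. The article misdescribes a log-link beta as a cost difference and bases the ICER and ICUR on it. Taken literally, the ratios would have no dollar unit. This conclusion rests on the algebra of the log link and on the stated wording, not on any assumed cost.

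The size of the error cannot be computed from the document. In the illustration, one beta is compatible with ratios from about $6,667 to $33,333 per quality-adjusted year; those figures depend on the assumed TAU means, cost ratio and effect. With a given effect, the direction of the ratio is preserved, because beta and the dollar increment share a sign.

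The consequence is confined to secondary question (b). The primary BAI analysis, the sample size and the data collection are untouched. The remaining uncertainty is whether an unseen analysis plan already computes dollar-scale costs; if so, only the article's wording is at fault.

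**What to change.** Replace the sentence on the ratios with text to this effect:

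1. **Numerator.** The incremental cost is the average difference in dollars between each participant's model-predicted cost under SMS + TAU and under TAU, taken from the adjusted log-link GLM (recycled predictions). Do not describe the beta itself as a cost difference.
2. **Denominator.** The effect is accumulated over the same period as the costs: anxiety-free days as already described, and AQoL-6D utility as the area under the curve, compared between arms with adjustment for baseline utility.
3. **Horizon.** The between-arm ratios use 12 months, as in secondary question (b), because TAU is offered the programme after that. Costs to 24 months can be reported within arm. Pairing 12-month effects with two-year costs would create a new mismatch.
4. **Uncertainty.** Intervals and sensitivity ranges refer to the dollar-scale increment and the resulting ratios.

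Optional additions are a statement of how zero costs are retained (for example a two-part model, or quasi-likelihood with robust standard errors) and a bootstrap of cost-effect pairs that respects the SMS groups.

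The cost is a few sentences and standard post-estimation code. No new data, visits or participants are needed.
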